## Method and analysis

The ES trial is a multicentre, parallel group, randomised controlled trial to examine the clinical, cost-effectiveness and safety of an ES performed in the mid-luteal phase of the preceding cycle prior to a first-time IVF/ICSI cycle. Eligible participants will be randomised to either the treatment-as-usual (TAU) arm, consisting of usual IVF treatment, or the intervention arm where ES will be performed followed by usual IVF treatment. The overall study design is illustrated below in the study flow chart (figure 1).

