#### Trial Design

The trial consists of two phases—an internal pilot to assess feasibility of recruitment and delivery of the intervention, and a 2-year main recruitment phase.

The trial will commence with a 9-month internal pilot recruitment phase across approximately six UK fertility units to justify whether or not the recruitment strategy and the scheduling of the ES procedure are feasible and will use the same trial procedures as described for the main trial.

The trial is collaboration between research staff at The Jessop Wing, Sheffield Teaching Hospital NHS Foundation Trust and The University of Sheffield—Clinical Trials Research Unit (CTRU) who is responsible for the conduct of the trial. Funding to run the trial has been awarded by the National Institute for Healthy Research HTA. At the end of the pilot phase, the trial steering committee (TSC) will report to the funder on whether the feasibility criteria have been met and whether the trial should continue.

The trial will be conducted in compliance with the approved protocol, Good Clinical Practice and regulatory requirements. Main trial recruitment commenced on January 2017 and is ongoing.

Sheffield CTRU will aggregate feasibility of the research and intervention protocols. The trial will be considered infeasible and will be stopped if either of the following conditions apply:Feasibility of recruitment to the main trial: defined as recruitment of fewer than 108 participants (75% of the 144 target) during the internal pilot phase.Scheduling of the ES procedure: defined as less than 75% of women scheduled to receive their ES procedure have received the ES at the correct time point.

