##### Trial intervention

ES is a minor procedure of 10–20 min duration that will be performed in an outpatient setting at local IVF centres in line with local procedures and the trial standard operation procedure (SOP). The participant will be required to use a barrier method of contraception (if necessary) during the menstrual cycle in which the ES will be performed. During ES, a speculum is inserted into the vagina and the cervix exposed and cleaned. A pipelle or similar endometrial sampler is then inserted into the cavity of the uterus; negative pressure is applied by withdrawal of the plunger. The sampler is rotated and withdrawn several times so that tissue appears in the transparent tube. The sampler and speculum are then removed. If no tissue is seen in the transparent sampler, this is an indication that the sampler was not fully inside the uterine cavity and therefore the procedure is repeated. Following the procedure, women will complete a Visual Pain Scale (Likert) to assess their pain and tolerability assessment of the procedure within 30 min of the initial ES and then again at 24 hours and 7 days postprocedure via an automated text message.

Compliance to the intervention will be ascertained through the clinician or research nurse/midwife recording whether or not the patient has (1) attended the clinic for the ES procedure and (2) received the ES procedure as per protocol (PP). Any deviation from the protocol will be noted and reported as per the Sheffield CTRU SOP.

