### Statistical analysis

Primary analysis will be performed on the intention-to-treat population (all participants randomised into the trial). All statistical exploratory tests will be two tailed at 5% nominal level. Baseline demographic (eg, age), physical measurements (eg, BMI) and health-related data will be described and summarised overall and for both treatment groups. The women, not the IVF cycle, will be the unit of analysis. If the woman fails to get pregnant or does not have IVF treatment, they will be included in the analysis of the primary outcome as a negative outcome (ie, non-live birth). For sensitivity analyses, PP analyses will also be undertaken which will be defined as for ES participants in the intervention group, receiving the ES procedure as documented in the study protocol and undergoing IVF/ICSI in the subsequent menstrual cycle, including embryo transfer. For the control group, the PP population will receive IVF/ICSI including embryo transfer. Subgroup analyses will be undertaken to explore the effect of important variables related to the participant and their treatment on the primary and secondary outcomes. These subgroups are:Day of embryo transfer (day 2, 3, 4, 5 or 6).Fertilisation method (IVF, IVF or ICSI, ICSI (spilt)).Type of protocol (long or antagonistic).Embryo transfer (single or double) and whether the embryo was fresh or frozen.Previous history of consecutive miscarriages (0–2 vs ≥3).

AEs will be reported as a proportion of all women randomised. AEs including SAEs will be compared between the two groups using a Fisher’s exact test, χ^2^ test or negative binomial regression model in case of repeated events per woman (as appropriate). A 95% CI for the difference in AE rate between the groups will also be calculated with associated point estimate depending on the method used.

Health economic results will be presented in the net-benefit framework and will allow for uncertainty using bootstrapping and probabilistic sensitivity analysis.

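### Adverse events are expressed per woman randomised, with no summary per woman who had the scratch, so procedural risk will be understated to the extent that allocated women do not have it

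*Protocol article*

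**What the plan says.** The Statistical analysis section of the protocol article gives one denominator for AEs: "AEs will be reported as a proportion of all women randomised". It then says that "AEs including SAEs will be compared between the two groups using a Fisher’s exact test" or an alternative test, and that "A 95% CI for the difference in AE rate between the groups will also be calculated". So the presentation is by randomised group, with a difference between groups.

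The same section describes a second population: "For sensitivity analyses, PP analyses will also be undertaken". In the intervention arm that set requires ES as the protocol describes it, IVF/ICSI in the next menstrual cycle, and embryo transfer. The article does not tie it to AEs.

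Three other places bear on the point.
- The Method and analysis section gives the trial's subject as the "clinical, cost-effectiveness and safety of an ES performed in the mid-luteal phase of the preceding cycle", and the Discussion expects the trial to determine whether ES is safe and well tolerated.
- The Trial intervention section says that staff record attendance and whether the woman "received the ES procedure as per protocol (PP"; deviations are noted as well.
- The Trial Design section would stop the trial as infeasible if, in the pilot, "less than 75% of women scheduled to receive their ES procedure have received the ES at the correct time point".

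**The concern.** Safety of the procedure is a stated aim, and a woman who is offered ES wants to know the risk if she has it. The Background names the procedural hazards as period-like discomfort during ES and possible intrauterine infection. Only women who undergo ES are exposed to these. Each woman allocated to ES who does not have it adds one to the denominator and nothing to the numerator, so the rate moves towards apparent safety.

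Some non-receipt is foreseeable from the article itself. Randomisation is allowed until IVF starts, ES may require IVF to be delayed, and spontaneous pregnancy between randomisation and IVF is anticipated. If the only published figure is per woman randomised, readers may take it as the risk of the procedure.

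**Working it through.** **Is there a figure in the plan to reproduce?** Not for this point: the article states no AE rate or complication risk. The only planned number needed is the arm size. The Sampling section's 496 per group reproduces with a continuity-corrected two-proportion calculation (30% against 40%, 90% power, two-sided 5%). Then 992 / 0.95 = 1044.2, in line with the stated 1044. With 1:1 allocation, 1044 / 2 = 522 women per arm.

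**Which sets does the article define, and does either equal the women who had ES?**
- All randomised: includes women in the ES arm who did not have it.
- Per protocol: leaves out women who had ES but whose IVF was not in the next cycle, or who had no embryo transfer. A woman whose IVF was delayed by an ES complication would be among those left out.

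Neither set is the group exposed to the procedure. One includes unexposed women and the other drops some exposed women.

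**Dilution.** Let r be the complication risk per woman who had ES, and u the proportion of the ES arm that had it. Both are assumptions.

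Expected events = r × u × 522, so the rate per woman randomised to ES = r × u, and the relative understatement = 1 − u.

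| Assumed uptake | Women who had ES | True 1% appears as | True 4% appears as | True 10% appears as |
|---|---|---|---|---|
| 75% | 391.5 | 0.75% | 3.0% | 7.5% |
| 90% | 469.8 | 0.90% | 3.6% | 9.0% |
| 100% | 522 | 1.0% | 4.0% | 10.0% |

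With women who had ES as the denominator, every row returns the true risk. The scaling applies only to events that the procedure causes; background events in pregnancy or IVF are not reduced in this way.

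**Between-group difference.** With a proportion c of controls having ES elsewhere, the expected difference due to ES is r × (u − c). For r = 4%, u = 75% and an assumed c = 5%, this is 4% × 0.70 = 2.8 percentage points. That is a correct estimate of the effect of allocation, but it is not the risk per procedure.

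**Precision if no event is seen.** The exact two-sided 95% upper limit is 1 − 0.025^(1/n). For n = 522 it is 0.70%; for n = 392 (75% of 522, rounded) it is 0.94%. The article plans no single-arm interval, so this shows only that the choice of denominator also affects how reassuring an absence of events looks.

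**The case against.** The strongest reply is that the article fixes a valid analysis and rules out nothing further. It is a condensed account that refers readers to the full protocol, and the analysis plan is not shown. A table by procedure received may well be there. That stands as a limit: the article does not say that the randomised denominator is the only one. But the denominator is a stated rule, not a missing detail, and a plan written to follow it would inherit it.

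A reader might infer four stronger things, none of which the article supports.
- *That the trial states a procedural risk, or a precision for it, that is too favourable.* It states neither.
- *That control women dilute the ES rate.* Pooling both arms would do that, but the plan compares the two groups. Only non-recipients within the ES arm matter.
- *That the design accepts a quarter of women going without ES.* The 75% criterion is a pilot stopping rule about timing. A woman who has ES off schedule fails it but carries the full procedural risk and dilutes nothing. It is not an expected uptake.
- *That the randomised AE comparison is biased towards no harm.* It estimates the effect of allocation validly. Moreover, the post-procedure AE enquiry is made only in the ES arm, which could raise that arm's count, so the net direction in the comparison is not established.

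Two further points are fair. Pain and tolerability are rated after the procedure, so by women who had it, although this gives no complication rate. And the Safety section describes seriousness and expectedness but no judgement of relatedness to ES, so an added table cannot rest on one.

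**Conclusion.** The point holds in a limited form. The stated denominator does not answer the question of what risk a woman takes by having ES, and neither population in the Statistical analysis section does so. A complication rate taken from the ES arm will be too low by a relative 1 − uptake: 25% at an assumed 75% uptake, 10% at 90%, and nothing at full uptake. For a true 4%, that is at most 1.0 percentage point over the range considered.

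This rests on assumed values for uptake and risk, and on the events concerned being ones that only recipients can have. It does not touch the primary outcome or the validity of the randomised AE comparison. It is a cheap improvement of modest size to how procedural safety is reported.

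**What to change.** Keep the comparison in all women randomised. Add to the Statistical analysis section that:
1. AEs and SAEs are also tabulated by procedure actually received;
2. events recorded from the ES procedure up to the start of IVF are reported per woman who received ES, with the number who received it and an exact two-sided 95% confidence interval;
3. any statement about procedural safety cites this figure beside the randomised comparison.

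Count as recipients all women who had the procedure, including those who had it off schedule. Defining the events by time window avoids the need for a relatedness judgement, but assumes that event dates are recorded.

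The cost is one extra table. Receipt of ES in the trial is already recorded, as is ES received elsewhere. The downside is a slightly less favourable figure that has no randomised comparator and, being defined by a time window, may include some events not caused by ES.

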##### Sampling

The primary outcome is the LBR. This is defined as a live birth after completed 24 weeks gestation, within the 10.5-month post-egg collection follow-up period. This time period will enable the collection of any neonatal deaths (up to 6 weeks post partum). The denominator for calculating the LBR will be the number of women randomised to each group. Data from the HFEA suggest an LBR of 32.8% in women under 35% and 27.3% in women aged 35–37. The sample size calculation assumes a 30% LBR in the control group and that an absolute increase of 10%, to a 40% LBR (a relative risk of 1.33) in the intervention groups is of clinical and practical importance. The effect size, a 10% absolute difference in LBR, we are proposing is large, but we believe an effect of such magnitude is needed to change clinical practice (there is a 5% absolute difference in LBR between women aged under 35 and 35–37) and is less than that observed in the systematic reviews described above (where, at the time of sample size calculation, the relative risk estimates for live birth ranged from 1.83 to 2.46).^2 17^ To have a 90% power of detecting this difference or more, in LBR rates between the groups, as statistically significant at the 5% two-sided level, will require 496 women per group (992 in total). Adjusting for a predicted drop-out rate of 5% (due to anticipated difficulties of follow-up for patients who have been referred from NHS Trusts other than the participating fertility unit), we will require 1044 participants.

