##### Safety considerations, safety monitoring and AE reporting

All AEs and serious AEs (SAEs) will be recorded by the local research team at each fertility unit. All AEs/SAEs will be followed up until satisfactory resolution or until the treating clinician and the principal investigator (PI) deems the event to be chronic or the participant to be stable. Research nurses/midwives will ask patients for any details of AEs at five time points: post procedure (if randomised to receive ES), at the participants’ pregnancy test, and then, if pregnancy has been achieved, at 3 and 6 months post-egg collection and finally 6 weeks post partum.

AEs/SAEs will be collected up to the participants’ final study-related follow-up event. If embryo transfer does not occur, the research nurse/midwife will contact the participant approximately 2 weeks after egg collection to identify if any AEs have occurred. In the case of a negative pregnancy test, the site research team should make every effort to obtain AE data from the patient or the medical notes at routine clinical care contacts; no further contact will be made outside of routine clinical care.

Expected AEs will be those which occur regularly due to pregnancy, and expected SAEs are those events which are expected in the patient population as a result of the routine care/treatment of a patient. Expected SAEs and all AEs will be collected as part of the trial and entered into the electronic case report form, but will not be reported to regulatory bodies (NHS REC/sponsor).

Unexpected SAEs will be reported to the Sheffield CTRU as soon as staff at the fertility units become aware of the event.

All SAEs will be reviewed by the data monitoring and ethics committee (DMEC) and trial management group (TMG) at regular intervals. The chief investigator will inform all PIs concerned of relevant information that would adversely affect the safety of the participants.

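### The all-randomised adverse event comparison rests on unequal enquiry between the arms, so an excess with ES could reflect extra asking or more pregnancies as well as harm

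*Protocol article*

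**What the plan says.** Under Safety considerations, safety monitoring and AE reporting, the article states: "Research nurses/midwives will ask patients for any details of AEs at five time points: post procedure (if randomised to receive ES". The second time point is the pregnancy test. The other three (3 months, 6 months and 6 weeks post partum) apply only if a pregnancy has been achieved. A woman who has no embryo transfer is contacted about two weeks after egg collection, in either arm. After a negative test the site is to make every effort to get AE data from the woman or her notes at routine contacts, but "no further contact will be made outside of routine clinical care". The Follow-up section treats the study as complete for a woman with no confirmed pregnancy. The same safety section counts events that commonly arise from pregnancy as expected AEs, and all AEs are collected.

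The Statistical analysis section then says: "AEs will be reported as a proportion of all women randomised. AEs including SAEs will be compared between the two groups". It names Fisher's exact test, a chi-squared test or, for repeated events, negative binomial regression, with a 95% CI for the difference in AE rate. It states no common observation window, exposure adjustment or separation by period. The Blinding section provides no sham procedure, so the control arm has no visit to match the scratch visit.

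**The concern.** A between-arm AE test shows harm cleanly only if events are looked for alike in both arms. Two features of the schedule prevent this.

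- **An enquiry in one arm only.** Background events that surface at the post-procedure visit have no control counterpart. This applies even if ES does nothing.
- **Enquiries that depend on an outcome.** Pregnant women are asked three more times over many more months, and pregnancy itself produces recordable AEs. If ES raises the pregnancy rate, more women in that arm enter this longer follow-up.

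The Method and analysis section names safety as something the trial examines, and the Discussion says the trial will determine whether ES is safe and well tolerated. A significant AE excess would bear on that statement, yet the planned test could not say how much of it came from the procedure, from pregnancy or from asking more often. The primary outcome is not affected.

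**Working it through.** **1. The plan's own figure.** The article gives no AE rate and no power for AEs. Its only calculation is the sample size, which supplies the rates and arm sizes used below. "The sample size calculation assumes a 30% LBR in the control group", with "an absolute increase of 10%, to a 40% LBR (a relative risk of 1.33) in the intervention groups". The power is 90% ("To have a 90% power of detecting this difference or more") at the two-sided 5% level.

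- Without continuity correction: n = [1.960 × √(2 × 0.35 × 0.65) + 1.282 × √(0.30 × 0.70 + 0.40 × 0.60)]² / 0.10², which gives 477 per group.
- With continuity correction: 496 per group, 992 in total, as stated.
- With 5% drop-out: 992 / 0.95 = 1044.2, against 1044 stated, so 522 per arm.

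The sample size reproduces and is not in dispute.

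**2. Scheduled AE enquiries per woman.** Let p be the probability of pregnancy. Assume every woman has one common contact: the pregnancy test or the contact two weeks after egg collection.

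- Control: 1 + 3p
- ES: 2 + 3p

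The planning live birth rates stand in for p. They are a low stand-in, because not every pregnancy ends in a live birth.

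| Scenario | Enquiries per woman | Relative to control |
|---|---|---|
| Control, p = 0.30 | 1 + 0.90 = 1.9 | – |
| Inert ES, p = 0.30 | 2 + 0.90 = 2.9 | 2.9/1.9 = 1.53 |
| ES effective as planned, p = 0.40 | 2 + 1.20 = 3.2 | 3.2/1.9 = 1.68 |

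For an inert ES the whole gap is the single post-procedure enquiry. For an effective ES both routes contribute.

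**3. What this could do to the test (illustration only).** Assume that ES does no harm and that each enquiry has the same chance q of yielding a recorded AE in both arms. Then, with k = 1 (control) or 2 (ES),

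P(at least one AE) = (1 − p)[1 − (1 − q)^k] + p[1 − (1 − q)^(k+3)].

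At q = 0.05:

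- Control: 0.70 × 0.0500 + 0.30 × 0.1855 = 9.1%
- Inert ES: 0.70 × 0.0975 + 0.30 × 0.2262 = 13.6%
- Effective ES: 0.60 × 0.0975 + 0.40 × 0.2262 = 14.9%

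The approximate chance of a significant difference at the two-sided 5% level, with 522 per arm, depends on how much the ES-only enquiry adds:

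| Assumption about the ES-only enquiry | Inert ES | Effective ES |
|---|---|---|
| Adds as many new events as any other (q = 0.02 to 0.20) | 31% to over 99% | 46% to over 99% |
| Adds nothing beyond what the common contact elicits | nominal 5% | 7% to 27% |

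The upper row is an extreme, because it treats enquiries as independent and gives no credit to recall or case notes. The lower row is the opposite extreme for the ES-only enquiry. The article does not say where between them the trial would fall.

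**The case against.** Several points on the other side have force.

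- **Collection does not stop after a negative test.** Sites must still seek AE data at routine contacts or in the notes, and unexpected serious events are reported whenever staff learn of them. This stands and narrows the gap, but it does not make ascertainment equal.
- **Contacts are not events.** A reader might infer from 68% more enquiries that recorded AEs would be inflated by a similar amount. The article does not support that. Both arms are asked at the pregnancy test, and nothing confines that question to recent events, so an earlier ES enquiry may partly record what would have been reported anyway.
- **Part of any excess is real.** Discomfort or infection after the scratch is a true harm, and extra pregnancy events under an effective ES are a true consequence of assignment. The all-randomised comparison is therefore a legitimate total effect. The difficulty is what it can be taken to mean.
- **Some of this is already separate.** Pain and tolerability are collected on their own in the ES arm, and miscarriage, ectopic pregnancy, stillbirth, preterm delivery and multiple birth are distinct secondary outcomes. General AEs are not separated in this way.
- **AE windows and offsets are commonly left to the SAP.** That is true, and an unseen SAP may deal with this. The point does not rest on an omission: the article itself fixes the enquiry schedule, the denominator and the between-arm tests, and together they create the problem.

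**Conclusion.** The concern holds in a limited form. The stated comparison mixes procedure harm, consequences of pregnancy and unequal asking. The contact imbalance is about 1.9 against 2.9 or 3.2 scheduled enquiries per woman. It assumes one common contact for everyone and live birth rates as a stand-in for pregnancy rates. Extra asking and, if ES works, extra pregnancies push towards more recorded AEs in the ES arm. The size cannot be fixed from the article: the illustration runs from almost no effect to a near-certain significant difference, depending on an AE rate and a degree of recall that are not given.

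Two stronger readings should be avoided. One is that the planned test is simply invalid: it estimates a real total effect of assignment. The other is that the randomised safety comparison should begin at the start of IVF. ES takes place in the preceding cycle, so that start would remove the procedure window from the only randomised safety comparison.

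**What to change.** Keep the all-randomised comparison of AEs and serious AEs, describe it as the total effect of assignment, and state that unequal ascertainment affects it. Add an analysis by period:

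1. **Randomisation to the common contact.** Compare the arms over all women randomised, counting AEs from randomisation to the pregnancy test or the contact two weeks after egg collection. Base the comparison on the enquiry made in both arms. The window includes the procedure. Flag events recorded only at the ES-only visit, and show the result with and without them. This is the comparison to interpret for safety.
2. **Post-procedure events.** Report these descriptively for the ES arm.
3. **Pregnancy-period events.** Tabulate these separately, per woman randomised and among pregnant women. Label the second table non-randomised, because pregnancy is a post-randomisation outcome. Use follow-up time as an offset in any rate model.

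The cost is a change of wording, a few extra tables and a less simple safety summary. No new contacts are needed, provided the case report form records when each event began and at which contact it was reported. The article does not say whether it does.

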##### Randomisation

The randomisation schedule will be generated by Sheffield CTRU prior to the start of the trial; access to the schedule will be limited only to the trial statistician. The randomisation sequence will be computer generated and stratified by site and protocol (antagonist or long protocol). Random permuted blocks of variable size will be used to ensure enough participants are allocated evenly to each arm of the trial at each site. Research staff at recruiting centres will be unable to access the randomisation sequence and will use a web-based computer system with restricted access rights to enter participant details; randomisation outcome will then be revealed. Re-randomisation will not be permitted.

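### Adverse event proportions are compared with tests that ignore the randomisation strata: valid, mildly conservative if sites differ, and improved at almost no cost

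*Protocol article*

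**What the plan says.** The Randomisation section of the protocol article fixes the design: "The randomisation sequence will be computer generated and stratified by site and protocol (antagonist or long protocol"), with random permuted blocks of variable size and 1:1 allocation. The Recruitment section plans 16 units, so there are up to 16 × 2 = 32 strata.

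The Statistical analysis section fixes the safety summary and its methods. On the denominator it says: "AEs will be reported as a proportion of all women randomised". For the comparison of the arms, serious events included, it lists three methods. Two are for proportions, namely Fisher's test and chi-square. The third is for counts, a "negative binomial regression model in case of repeated events per woman (as appropriate"). On the interval the section adds: "A 95% CI for the difference in AE rate between the groups will also be calculated with associated point estimate depending on the method used".

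On ascertainment, the safety section says: "All AEs and serious AEs (SAEs) will be recorded by the local research team at each fertility unit".

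**The concern.** Fisher's exact test and the ordinary chi-square test compare two pooled groups. Neither uses site or protocol, the factors within which the arms are balanced.

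Blocked allocation gives each site nearly equal numbers in the two arms. A site that records many AEs therefore raises both arms alike, and its level cancels from the difference. The pooled variance p(1−p) still counts that between-site spread as error. If recording differs between local teams, the standard error is too large, the interval too wide and the p value too high.

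For a harm outcome, lost precision points the unwelcome way: a real excess in the scratch arm is somewhat harder to show. The Discussion expects the trial to say whether the procedure is safe and well tolerated, so the AE comparison supports a stated conclusion.

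**Working it through.** **Inputs from the article.** 1044 women, 1:1, so 522 per arm; 16 sites and two protocols; two-sided 5%. The total reproduces. For 30% v 40% at 90% power the uncorrected size is 477 per group; with continuity correction it is 496, as stated. Then 2 × 496 = 992 and 992/0.95 = 1044.2. The article gives no figure for the AE comparison itself.

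**Assumptions.** AE rates of 5%, 20% and 40%; an AE excess of 8 points (5 points at the 5% rate); site ICC ρ of 0, 0.05, 0.10 and 0.20.

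**Step 1: interval width.** The total variance per woman is p(1−p). The part left within sites is p(1−p)(1−ρ). With blocks within sites, only the second contributes to the true error. The unstratified standard error is therefore too large by the factor k = 1/√(1−ρ).

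**Step 2: level.** The chi-square test's actual level is 2[1 − Φ(1.96k)].

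**Step 3: power, 40% v 48%.** The unstratified SE is √[(0.40×0.60 + 0.48×0.52)/522] = 0.0306, so z = 0.08/0.0306 = 2.61. Chi-square power is Φ[(z − 1.96)k]; stratified power is Φ(zk − 1.96).

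| ρ | k | chi-square level | chi-square power | stratified power | gain, points |
|---|---|---|---|---|---|
| 0 | 1.000 | 5.0% | 74.3% | 74.3% | 0 |
| 0.05 | 1.026 | 4.4% | 74.8% | 76.4% | 1.6 |
| 0.10 | 1.054 | 3.9% | 75.4% | 78.6% | 3.2 |
| 0.20 | 1.118 | 2.8% | 76.7% | 83.2% | 6.5 |

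**Step 4: check by simulation.** The set-up was 1044 women, 16 unequal sites, blocks within site × protocol, and CMH over 32 strata. Simulation error is about 0.9 points.
- SE ratio, unstratified to Mantel-Haenszel: 1.00, 1.02, 1.05 and 1.11 at ρ = 0, 0.05, 0.10 and 0.20.
- Chi-square v CMH power at a 40% rate: 73.4 v 74.7% (ρ = 0.05), 75.4 v 78.0% (0.10), 75.3 v 81.7% (0.20).
- The same at a 20% rate: 86.9 v 87.8%, 87.6 v 89.3%, 89.1 v 92.0%.
- At a 5% rate CMH held its level (4.6–5.3%) and lost no power, so 32 strata are not too sparse for it.

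**Step 5: separate Fisher's own conservatism.** With no site variation at all, 522 per arm and a 40% rate, Fisher rejects a true null 4.3% of the time against 5.0% for chi-square. Its power for 40% v 48% is 71.9% against 74.0%. About 2 points of any Fisher-to-CMH gap therefore come from discreteness. Chi-square is the like-for-like comparator.

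**Step 6: how extreme is each ICC?** Take site rates as Beta with parameters 0.4(1/ρ − 1) and 0.6(1/ρ − 1). The 5th to 95th percentiles of site AE rate are then 23–59% at ρ = 0.05, 16–67% at 0.10 and 8–79% at 0.20.

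**Step 7: a second scale.** Let stratum rates vary on the logit scale instead. An SD of 0.5 widens the interval by 0.2% to 2.4% over AE rates of 2–30%. At a 10% rate the half-width is 3.77 v 3.73 points, and power for a 5-point excess is 68.2 v 68.9%. An SD of 1.0 widens it by 2–9%.

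**The case against.** The best case for leaving the text alone has four parts.

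- **The named tests are valid and customary.** Their error rate is at or below 5% apart from simulation noise, and nothing in the article promises a stratified AE analysis. A reader might infer that the Randomisation and Statistical analysis sections contradict each other, or that the AE tests are invalid. Neither follows: this is a question of efficiency.
- **The article does not say the negative binomial model is unadjusted.** It can carry site and protocol as covariates without changing a word, and a condensed article may leave covariates to the full protocol or analysis plan. A reader might infer an unadjusted model, but that would rest on silence alone. This stands, and no loss is claimed for that model.
- **Large between-site variation is not documented.** AEs are asked for at set time points at every unit, and the patient and public involvement section reports a request for a common follow-up proforma. This stands as a limit on size, and it is why ICC 0.20 is treated as extreme.
- **Safety does not rest on an end-of-trial p value.** The monitoring committee reviews all SAEs, receives monthly AE reports and may advise stopping. A reader might infer that harm would go undetected; the article does not support that. The monitoring does not, however, supply the final reported comparison and its interval.

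An objection that 32 strata make stratified analysis unstable does not stand for common events (step 4). For rare events the proposal keeps Fisher's test.

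**Conclusion.** The point holds as a free improvement, not as an error. Fisher and chi-square ignore the strata used in randomisation, and the direction of the effect is conservative.

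With site ICC between 0 and 0.10, the unstratified interval is about 0–5% too wide and chi-square loses about 0–3 points of power against CMH. At ICC 0.20 this becomes about 10% and 3–6 points, and chi-square's actual level falls to about 3%. With no site variation nothing is lost by chi-square. All of these figures depend on assumed AE rates and ICCs, because the article states neither.

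**What to change.** In the Statistical analysis section, or in the analysis plan that implements it:

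- For AEs and SAEs common enough to stratify, compare proportions with a Cochran-Mantel-Haenszel test and report a Mantel-Haenszel risk difference with 95% CI, stratified by site and protocol.
- Keep Fisher's exact test for rare event types.
- If negative binomial regression is used for repeated events, state that site and protocol are included as covariates (a clarification).

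The cost is a sentence or two of wording. Both factors are already in the randomisation data. The one drawback is that strata without a contrast (women in only one arm or, for the test, no events) carry no weight, which is negligible for common AEs.
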